## Abstract

**Background:**

Declining physical activity is associated with a rising burden of global disease. There is little evidence about effective ways to increase adherence to physical activity. Therefore, interventions are needed that produce sustained increases in adherence to physical activity and are cost-effective. The purpose is to assess the effectiveness of a primary care physical activity intervention in increasing adherence to physical activity in the general population seen in primary care.

**Method and design:**

Randomized controlled trial with systematic random sampling. A total of 424 subjects of both sexes will participate; all will be over the age of 18 with a low level of physical activity (according to the *International Physical Activity Questionnaire*, IPAQ), self-employed and from 9 Primary Healthcare Centres (PHC). They will volunteer to participate in a physical activity programme during 3 months (24 sessions; 2 sessions a week, 60 minutes per session).

Participants from each PHC will be randomly allocated to an intervention (IG) and control group (CG). The following parameters will be assessed pre and post intervention in both groups: (1) health-related quality of life (SF-12), (2) physical activity stage of change (Prochaska's stages of change), (3) level of physical activity (IPAQ-short version), (4) change in perception of health (vignettes from the *Cooperative World Organization of National Colleges, Academies, and Academic Associations of Family Physicians*, COOP/WONCA), (5) level of social support for the physical activity practice (*Social Support for Physical Activity Scale*, SSPAS), and (6) control based on analysis (HDL, LDL and glycated haemoglobin).

Participants' frequency of visits to the PHC will be registered over the six months before and after the programme. There will be a follow up in a face to face interview three, six and twelve months after the programme, with the reduced version of IPAQ, SF-12, SSPAS, and Prochaska's stages.

**Discussion:**

The pilot study showed the effectiveness of an enhanced low-cost, evidence-based intervention in increased physical activity and improved social support. If successful in demonstrating long-term improvements, this randomised controlled trial will be the first sustainable physical activity intervention based in primary care in our country to demonstrate long-term adherence to physical activity.

**Trial Registration:**

A service of the U.S. National Institutes of Health. Developed by the National Library of Medicine. ClinicalTrials.gov ID: NCT00714831.

## Background

People who lead a physically active life or are in good physical shape have a lower mortality rate and a longer life expectancy [1,2]. The regular practice of physical activity (PA) has a positive effect in reducing obesity and preventing cardiovascular pathologies [3,4], reducing the risk of stroke [5], reducing the deterioration of the pulmonary function and the risk of suffering EPOX [6], prevents diabetes [7], increases HDL cholesterol and decreases triglycerides and total cholesterol [8]. It is also important in preventing falls in the elderly [9], generates a sensation of well-being, reduces anxiety and symptoms of depression, increases self-esteem [10], and improves the perception of quality of life related to health [11,12]. The World Health Organisation (WHO) has published a report in which physical inactivity is cited as one of the principle risk factors in the development of chronic illness and cause of death, especially in industrialised countries [13]. Even so, only 18% of the European population claims to practice moderate physical activity on a daily basis [14]. According to the National Health Survey of 2001, 46.6% of the Spanish population over the age of 15 does not exercise in their free time and only 8.5% exercise on a regular basis [15]. Furthermore, data from the Catalan Health Survey of 2006 indicate that less than 48% of the Catalan population exercises sufficiently to improve their health, a percentage which has increased since the surveys of 1994 and 2002 [16]. The virtual absence of a public health practice infrastructure for the promotion of PA at a local level presents a critical challenge to control policy for chronic disease, particularly obesity. Translating the increasing evidence of the value of PA into practice will require systemic, multilevel, and multisectorial intervention approaches that build individual capability and organisational capacity for behaviour change, create new social norms, and promote policy and environmental changes that support higher levels of energy expenditure across the population [17].

In 2005, the Spanish Ministry for Health and Consumption designed the Strategy for Nutrition, Physical Activity and Prevention of Obesity (NAOS) with the aim of promoting a healthy lifestyle [18]. To the same end, in Catalonia, the Department of Health of the Catalan Government launched an integrated plan for the Promotion of Health through Physical Activity and Healthy Diet (PAAS) [19].

Within this plan, encouraging PA promotion in PHC is outlined as a priority [19], as in Spain the high proportion of inactive primary care patients (at least 70%) justifies the need to develop a targeted strategy for physical activity promotion in general practices [20]. There is contradictory evidence about the effectiveness of including the usual advice on the practice of regular physical activity in the consulting rooms of PHC [21-23], and it is not certain if it is even applicable in our country [24].

In Catalonia, Puig-Ribera, McKenna and Riddoch (2005) indicated that medical recommendations for physical activity were limited, basically due to lack of time, unfavourable working conditions in healthcare centres and lack of knowledge on the part of the healthcare professionals, making it clear that the task of promoting physical activity was not seen as effective; concluding with the importance of establishing working protocols for consultants to integrate the promotion of physical activity in their work on a daily basis in the clinical practice [25].

Several types of intervention for the promotion of PA in Primary Care have been reported. It has been demonstrated that those which combine written instructions, an exercise programme and strategies to change behaviour, and which are accompanied by several training sessions, are more effective [26]. Thus it appears that the highest success rate is seen in those interventions which are not limited to professional advice given at the PHC [26,27]. In the same way a systematic review concluded that advice in routine primary care consultations was not an effective strategy means of producing sustained increases in physical activity [28].

Various authors have indicated the importance of referring patients to professionals specialised in the design of healthy exercise programmes outside the healthcare environment, making use of the local resources available in each area as a strategy for effective integration of the promotion of exercise in Primary Care [17,29]. In this context, a recent systematic review [30] assessed whether exercise-referral schemes were effective in improving exercise participation in sedentary adults. These schemes showed a small effect on increasing physical activity in sedentary people, partly due to poor rates of uptake and adherence to the exercise schemes [30]. Therefore, further studies are required to find strategies to increase long-term adherence [31] by addressing the participation barriers such as lack of social support, intimidating environments to practice a regular physical activity and inadequate supervision [30].

A systematic review of interventions based on the promotion of walking found only two studies in which there was a significant increase in the time spent walking and which improved the clinical risk indicators [32]. Finally, a Cochrane review (2005) showed moderate but positive utility regarding the interventions based on self informed physical activity, such as the effect on the cardio respiratory state [33]. The effect of the interventions in achieving a predetermined threshold of physical activity was not significant with an odds ratio of 1.30 (Confidence interval 95%: 0.87 to 1.95) [33]. In better quality studies, exercise was self directed with some professional guidance and with constant professional support [29].

In 2006, Giné-Garriga and Martin developed a pilot study in Barcelona (with a control group) of the Programme for the Promotion of Physical Activity in the PHC in which they offered patients the possibility of participating for a three month period in an exercise programme carried out in their own healthcare centre [34]. Patients were recruited in the healthcare centres, and physical activity specialists designed programmes which were specifically aimed at the patients' needs [34,35]. The sessions were carried out together with nurses and physical therapists from the centre. The programme was carried out in the centre itself, making use of nearby outdoor public spaces in order to offer the patients convenient and familiar surroundings. During the last sessions of the programme all the participants were given information about the nearest municipal facilities and the activities offered, and a visit to these facilities was organized. Thus, the programme acted as a means for incorporating participants in local facilities once they had experienced the benefits of doing regular exercise and at the same time used behavioural strategies [36], accompanied by people from the same neighbourhood with similar needs [34].

In order to achieve this objective, establishing a link between the PHC and the central offices of the various municipal districts was considered essential, as was contact with local sports centres, civic centres and other health centres, in order to facilitate the incorporation of the patient in a programme or exercise session, either individual or group, outside the environment of the healthcare centre. Facilitating access to the existing local resources in the area would contribute considerably to the continuity of the initiatives and programmes being developed by Primary Care. Furthermore, it would encourage a greater number of citizens to establish a common protocol of action [28].

## Method and design

### Aim

This randomised controlled trial was designed to assess the effectiveness of a primary care physical activity intervention, which considered community strategies coordinated with municipal resources and the incorporation of various professional disciplines, in increasing adherence to physical activity in the general population seen in primary care.

### Study population

Inclusion criteria will include (a) adult patients (over the age of 18) of both sexes who will be seen at the PHC for whatever reason; (b) with a low level of physical activity as established by the shortened version of the questionnaire *International Physical Activity Questionnaire *(IPAQ) [37]; (c) with a diagnosed chronic pathology; (d) who will be willing to participate in an exercise programme; and (e) who will have minimum physical aptitudes to follow the programme (being able to walk and stand up from a chair independently).

Exclusion criteria will be based on certain medical conditions which could result in unwanted effects in older adults, such as the presence of unstable angina, uncontrolled congestive heart failure, unstable arrhythmia or heart valve disease, progressive or debilitating medical conditions, and severe hypertension (systolic ≥ 200, or diastolic ≥ 120) [38].

Written informed consent will be obtained from all subjects of both intervention (IG) and control group (CG). This trial was approved by the Clinical Investigation Ethics Committee of the IDIAP Jordi Gol, located in Barcelona.

### Recruitment process

Recruitment will take place in 9 PHC in different regions of Catalonia during the first three months of 2009. Until August 2008, 63 PHC in Catalonia were informed and the trial has been presented to the 54 centres which showed interest in participating. Of these, the first nine centres which volunteered to participate will undergo the trial. Two health professionals, who were selected on a voluntary basis from each of the participating centres, were trained. During the recruitment period, the opportunity to participate in the study will be offered daily to all patients with a chronic pathology, who by systematic random sampling will be previously identified in the doctors' lists: a total of 50 subjects per centre will be recruited. The patients who meet the inclusion criteria and agree to participate will be contacted to inform them about how the project will be carried out. A record of demographic and health data, as well as attendance at the sessions, will be kept of those who agree to participate in the intervention. Figure 1 shows the flowchart of participants' recruitment and trial design.

**Figure 1 F1:**
[figure not shown]
**Flowchart of participant's recruitment and trial design**.

### Randomisation

Previously trained professionals in each PHC will invite the subjects to participate in the study, following random systematic procedures during the recruitment period. All the subjects who meet the inclusion criteria must sign a consent form, carry out an initial evaluation and following this they will be randomly selected to form part of the IG or the CG. Random sequence generation will be computer-generated by an independent researcher, guaranteeing that the allocation groups remain confidential.

### Control group

Subjects assigned to the control group will be asked to continue their routine daily activities and will receive their usual care from their primary care practice. They will be given information and requested to give their informed consent. They will be invited to the first and the last session (3 months later) of the programme in which the different parameters will be evaluated. They will be reminded by telephone two months and three weeks prior post-intervention assessment session.

### Intervention

#### Physical activity promotion programme

When a patient agrees to participate an assigned professional health worker will send a registration form to the investigation team and to the specialist who will lead the exercise group. The patient will be contacted by telephone to carry out the evaluation and to start the intervention. All participants will report to the healthcare centre twice a week for 12 weeks, and all participants who hand in a consent form will undergo an analysis stating their intention to undergo the treatment.

Each session will last 60 minutes, and all protocols have been developed for progressive intensity. The sessions will be carried out by physical activity specialists in a room in the health centre itself, in nearby exterior locations (parks, squares, etc) or in municipal facilities in the same district. Table 1 shows the contents of the programme [35]. At the same time, participants will be shown exercises that they should do at home. It is recommended that from the first day, a minimum of three sessions per week be done at home without supervision and without keeping a record.

**Table 1 T1:** Components of the exercise programme [35]

**Component**	**Includes these exercises**	**Repetitions per exercise**^a^	**Duration of a single exercise or repetition**	**Duration per 60 minutes class**	**Major benefits**
**Warm-up**	- Range-of-motion. - Low-intensity aerobics.	4–8	2 seconds per repetition	10 minutes minimum	- Increases internal body temperature. - Injury prevention.

**Aerobics**	- Aerobic exercises (e.g. walking, swimming, cycling)	Varies	Varies	15–30 minutes	- Cardio respiratory endurance.

**Resistance training**	- Body- weight^b ^exercises. - Resistance exercises.	8–15	6 seconds per repetition	15–30 minutes	- Muscular strength and endurance.

**Cool-down**	- Stretching.	1	30–45 seconds per stretch	5–30 minutes	- Improved flexibility.

	- Relaxation techniques. - Stress-reduction techniques.	Varies	Varies	5–30 minutes	- Relaxation, stress reduction.

^a^Several factors determine the number of repetitions, such as the component of exercise, the level of fitness of the participant, the level of progress for that exercise, day-to-day variations in the participant's state, and the total amount of time available for the exercise class.

^b^Body-weight exercises are exercises in which one's body weight, such as the weight of one's arm or legs, serves as the resistance.

To facilitate continuity in the carrying out of physical exercise once the programme has finished, all participants will be offered a personalised exercised programme with exercises that have been performed during the sessions so that the subject can continue the activity as a matter of habit. Moreover, a list of local resources (sports facilities, civic centres, etc.) in the same district where the activity can be continued on a regular basis will be given. At the same time the penultimate session of the intervention will be carried out in a nearby sports facility with a previously programmed visit. During the first and last sessions, a baseline and final evaluation of the variables to be studied will be carried out.

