#### Other specific objectives

Secondary outcomes for IG and CG include: (a) decreasing the number of visits to the healthcare centre by individuals involved in the programme, registering the total number of visits during the six months before and after the programme; (b) description of the development of quality of life related to health, measured with SF-12 test [39,40] (the first and last session of the programme) and evaluation of short, medium and long term evolutions, with follow up at three, six and twelve months after the programme has finished; c) description of the evolution of perceived health status, measured with the COOP/WONCA vignettes (first and last session of the programme) [41]. This instrument showed good validity and reliability in general population in a previous study [41]; (d) evaluation of the attitude towards the change in behaviours in relation to regular exercise using the Prochaska scale (first session and six and twelve months after finalising the project) [42]; (e) evaluation of the social support for the physical activity practice, assessed using the SSPAS scale [43] (first and last session of the programme and three, six and twelve months after finalising the intervention). Reliability and validity of the scale was previously assessed in an elderly population [43]; and (f) description of the evolution of HDL, LDL and glycosilate hemoglobin (first and last session and 6 and 12 months after finalising the programme). Demographic and health data will be also collected (age, blood pressure, heart beat when resting, weight, height, body mass index, current medication and associated pathologies).

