### Sample size

Accepting an alpha risk of 0.05 and a beta risk of 0.20 in a bilateral contrast, 424 individuals are needed: 212 individuals in the IG and 212 in the CG in order to detect a difference equal to or higher than 0.15 between the two [23]. A proportion of 0.5 in one of the groups is to be assumed. A dropout rate of 16% is estimated, based on the pilot study experience [34].

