### Statistical methods

Analysis of effectiveness will be made followed by the intention to treat analysis. The analysis of data will be made using the SPSS statistic software version 15.0 and STATA, version 9.1. In all cases a bilateral alfa error of 0.05 will be used and the confidence intervals will be calculated at 95%. Descriptive statistics will be calculated and intervention and control groups will be checked for health and outcome measures at baseline.

A baseline comparability analysis of the CG and IG in relation to the variables studied, will be carried out. An s-Student test or ANOVA will be used in the comparison of means if the variables follow a normal distribution and the U of Mann Whitney if they do not. For the other dimensions of the analysis, a covariance analysis (ANCOVA) for repeated measures will be carried out.

For the multi-variance analysis the change in the time of the described dependent variables will be evaluated, and comparisons between the CG and IG will be established. To do this multilevel linear models will be adjusted, one for each dependent variable. In the first level the individual path or the evolution of each individual over a long period of time (pre-post intervention, 3,6,12 month follow-up) will be modelled. In the second level it will be adjusted according to the variables that refer to the individual; the intervention variable will be added (intervention or control) to the independent variables described earlier.

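### The end-of-programme evaluation is held at the last exercise session with a telephone reminder written for controls only, so outcome capture at that time point may depend on adherence in the intervention arm alone

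*Protocol article*

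**What the plan says.** **Where the outcome is taken.** The section on the physical activity promotion programme states: "During the first and last sessions, a baseline and final evaluation of the variables to be studied will be carried out". Under Other specific objectives, SF-12, SSPAS and the blood values carry the same first-and-last-session timing, with later measurements added. COOP/WONCA has no later measurement: "description of the evolution of perceived health status, measured with the COOP/WONCA vignettes (first and last session of the programme".

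**How controls are brought in.** The Control group section invites controls to the first and last sessions and adds: "They will be reminded by telephone two months and three weeks prior post-intervention assessment session".

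**How intervention patients are contacted.** The programme section describes one telephone contact, for the initial evaluation and the start of the sessions. It describes no call for the final evaluation.

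**Later follow-up.** Under Main objective, the primary IPAQ outcome is measured at baseline, at the end of the intervention and at 3, 6 and 12 months. The Blinding section has the later assessments done by visit or telephone, and the Abstract describes a face-to-face interview. Neither ties them to an exercise session.

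**Analysis.** Statistical methods says: "Analysis of effectiveness will be made followed by the intention to treat analysis". It also plans multilevel models over all time points.

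**The concern.** In the intervention arm the occasion for measurement is also a treatment session. Someone who has given up the sessions is no longer in the place where the outcome is collected, and the one reminder that is written down does not apply to that person. In the control arm there is nothing to give up, and the reminder does apply. The chance of having an end-of-programme value can therefore depend on adherence in one arm and not in the other.

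This matters because the primary outcome is itself adherence to physical activity, and people who leave an exercise programme are plausibly less active than those who stay. The Background cites poor uptake and adherence in exercise-referral schemes, so stopping is foreseeable. If such people are missing from one arm only, the programme can look better at its end than it is. Later rounds of follow-up can show a person's activity at 3, 6 or 12 months, but they cannot supply a value that was not taken at the end of the programme, and COOP/WONCA has no later round.

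**Working it through.** **1. Planning figures.** The Sample size section says: "Accepting an alpha risk of 0.05 and a beta risk of 0.20 in a bilateral contrast, 424 individuals are needed", with "212 individuals in the IG and 212 in the CG", in order to "detect a difference equal to or higher than 0.15 between the two". It adds: "A proportion of 0.5 in one of the groups is to be assumed". Dropout is given as one overall figure of 16%, not split by arm.

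For 0.50 against 0.65, two-sided 5%, 80% power:

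n = [1.96 × √(2 × 0.575 × 0.425) + 0.842 × √(0.25 + 0.2275)]² / 0.15² = 169.3, so 170 per arm, and 170/0.84 gives 203.

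With continuity correction:

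n = (169.3/4) × [1 + √(1 + 4/(169.3 × 0.15))]² = 182.4, so 183 per arm, and 183/0.84 gives 218.

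The stated 212 lies between the two, 2.8% below the corrected figure. It is taken as given. A random 16% loss leaves 212 × 0.84 = 178 per arm and power of about 0.82, so the question here is bias and not power.

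**2. Size of a possible bias.** The documents do not give the share of intervention patients who would be missed, or how active those patients are. Both are assumptions here.

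- True improved proportion: 0.50 in both arms (no effect).
- s: share of the intervention arm missed at the last session.
- q: improved proportion among those missed.
- Loss in controls: none, or 16% at random (178 left).

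The proportion seen among assessed intervention patients is p = (0.50 − s·q)/(1 − s), and the false gain is p − 0.50.

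The test statistic has mean Z = (p − 0.50)/√[p(1 − p)/(212(1 − s)) + 0.25/n_C], where n_C is the number of controls assessed.

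The two-sided type I error is 1 − Φ(1.96 − Z) + Φ(−1.96 − Z).

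Example with s = 0.16, q = 0.20, n_C = 212:

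- p = (0.50 − 0.032)/0.84 = 0.557, a false gain of 5.7 points.
- The standard error is 0.0506 and Z = 1.13.
- The type I error is about 20%.

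| s | q | p | False gain (points) | Type I error, controls complete | Type I error, controls 16% random loss |
|---|---|---|---|---|---|
| 0.16 | 0.10 | 0.576 | 7.6 | 33% | 30% |
| 0.16 | 0.20 | 0.557 | 5.7 | 20% | 19% |
| 0.16 | 0.30 | 0.538 | 3.8 | 12% | 11% |
| 0.16 | 0.40 | 0.519 | 1.9 | 7% | 6.5% |
| any | 0.50 | 0.500 | 0 | 5% | 5% |

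In the middle case the false gain is 5.7/15 = 38% of the target difference.

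**3. Sensitivity to the share missed** (q from 0.40 down to 0.10, 16% random loss in controls). With 8% missed, the false gain is 0.9 to 3.5 points and the type I error 5.3% to 10%. With 24% missed, they are 3.2 to 12.6 points and 9% to 66%. If controls lose the same share with the same selectivity, both arms shift equally and the bias is zero.

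**The case against.** The strongest reply is that the article nowhere excludes people who stop. A reader might infer from the last-session timing that stoppers lose their outcome and that the comparison is therefore biased towards the programme. The text does not support that:

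- Controls attend no exercise sessions and still come to the last one, about three months on. It is a scheduled event, and a patient who stopped could come in the same way.
- The Blinding section speaks of assessing participants, not attenders, and intention to treat is stated.
- Arrangements for tracing non-attenders may sit in the full protocol, which is not shown.
- The control reminder has an ordinary purpose: controls have no planned contact for three months, while intervention patients are due on site twice a week.
- Controls may also be lost selectively.
- The primary outcome is measured again at 3, 6 and 12 months away from sessions, and the multilevel models can use those values.
- The illustration puts all of its selective loss in one arm and tests completers at a single time point, which is not the planned model.

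All of this limits the point, and none of it removes it. The article does fix where the evaluation takes place and which arm is reminded. A reminder that offsets fewer visits among controls does nothing for an intervention patient who has stopped coming. Intention to treat and a multilevel model do not recover an unmeasured value. The model helps only so far as the observed data explain the loss, and a stopper's activity at week 12 is not observed. It would also be too strong to say that the procedure contradicts intention to treat: a value that might be missing is not a contradiction in the text.

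**Conclusion.** The point holds as a risk of unequal outcome capture between arms, not as a demonstrated bias. It concerns the end-of-programme comparison, which is one of the stated time points of the primary outcome, and COOP/WONCA, a secondary outcome with no later measurement. The IPAQ assessments at 3, 6 and 12 months are not affected by this mechanism.

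The likely direction favours the programme, provided that those missed are less active than those assessed and that controls show no comparable selective loss. With no true effect, 16% of the intervention arm missed and 10% to 30% of them improved, the false gain is about 4 to 8 points against a 15-point target, and the type I error about 11% to 33%. These figures borrow the protocol's overall dropout rate for one arm and assume the activity of those missed. They show what is possible and are not an estimate.

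This is a cheap and worthwhile improvement to the procedure, not an error that invalidates the design.

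**What to change.** In the programme and Control group sections, state that:

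1. the end-of-programme assessment is due for every randomised person at a fixed time, about 12 weeks after the programme starts at that centre, within a stated window and regardless of how many sessions were attended;
2. the same invitation and telephone reminders are used in both arms;
3. stopping the sessions is not withdrawal from follow-up;
4. anyone absent on the day is offered a catch-up date within the window, covering COOP/WONCA and the blood tests as well as IPAQ.

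The cost is a change of wording, about 212 reminder calls for each round of reminders in the intervention arm, and one catch-up date per centre. No additional patients or measurements are needed. It has to be settled before the programme ends, because a COOP/WONCA value missed then cannot be replaced.

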### Blinding – single blind

Baseline measures will be taken prior to allocation of randomisation. Independent investigators assessing participants at the end of the programme and at three, six and 12 month follow-up visits or phone calls will be blind to the allocation of the treatment group. Participants will be asked not to discuss group allocation with the assessing professional. Moreover, the person who carries out the analysis of the data will not be involved in the investigation.

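### Baseline is timed both before allocation and at the first programme session, to which already-assigned controls are invited; a last-session final evaluation also puts assessor blinding at risk

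*Protocol article*

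**What the plan says.** The protocol article times the baseline evaluation in two ways.

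**Before allocation.** Under Randomisation, eligible subjects sign consent, "carry out an initial evaluation and following this they will be randomly selected to form part of the IG or the CG". Under Blinding – single blind: "Baseline measures will be taken prior to allocation of randomisation".

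**At the first programme session.** Under Physical activity promotion programme: "During the first and last sessions, a baseline and final evaluation of the variables to be studied will be carried out". Under Control group, which opens with "Subjects assigned to the control group will be asked to continue their routine daily activities", those same subjects are "invited to the first and the last session (3 months later) of the programme in which the different parameters will be evaluated". Other specific objectives attaches first-session timing to the SF-12, COOP/WONCA, Prochaska stages, SSPAS and blood tests. The Intervention section also covers the evaluation and the start of training in one contact: "The patient will be contacted by telephone to carry out the evaluation and to start the intervention".

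For the end of the programme, the Blinding section says that independent investigators "will be blind to the allocation of the treatment group", and that participants are asked not to reveal their group to the assessor. The sentence in the Intervention section places that final evaluation in the last session.

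**The concern.** A baseline is protected by randomisation only if it is fixed before anyone can react to the allocation. The primary outcome is an increase in physical activity on the short IPAQ, judged by category or by weekly METs, and the IPAQ is a self-report. A participant who has just learned that he or she is in the exercise group, or is not, may answer baseline questions differently. In a change analysis that difference is indistinguishable from a treatment effect, and neither a larger sample nor later modelling removes it.

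The final evaluation raises a second, weaker issue. At the last class the intervention group is a set of people who have trained together for 12 weeks, while controls attend by invitation. An assessor working in that setting could infer the group without being told.

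**Working it through.** No figure in the protocol depends on this point, and the sample size is unaffected. The check is a comparison of the statements.

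**1. Can *first session* mean a visit before randomisation?**
- The Abstract gives 24 sessions at 2 per week. The Intervention section gives twice a week for 12 weeks: 2 × 12 = 24. The classes account for all 24 sessions, so none is left over as a separate assessment visit.
- Immediately before the sentence on baseline and final evaluation, the Intervention section places a sports-facility visit in the penultimate session of the intervention. First, penultimate and last therefore read as positions in one series: sessions 1, 23 and 24.
- The programme is given only to the intervention group, so its session 1 comes after allocation. The Control group section agrees: those invited to it are already assigned.

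On the plain wording, a session-1 baseline follows allocation, while the Randomisation and Blinding sections put baseline before it.

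**2. Which measures are affected?**
- *IPAQ.* The Main objective section says only that it is measured at baseline, at the end of the intervention and at three, six and twelve months. It gives no session label. The Intervention sentence, however, covers the study variables generally, so the IPAQ falls under it.
- *SF-12, COOP/WONCA, Prochaska stages, SSPAS.* Self-reported, with first-session timing stated explicitly.
- *HDL, LDL, glycated haemoglobin.* First-session timing, but not self-reported, so much less exposed.
- *Visit counts.* Registered over the six months before and after the programme, so not dependent on the session.

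**3. How would a shifted baseline enter the estimate?**
Let knowledge of allocation shift the mean reported baseline by d_I in the intervention arm and d_C in the control arm. The between-arm difference in change is

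(follow-up_I − baseline_I) − (follow-up_C − baseline_C),

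so it moves by −(d_I − d_C). If baseline is instead a covariate with slope b, the adjusted difference moves by −b(d_I − d_C). Neither expression contains the sample size. Statistical methods plans repeated-measures ANCOVA and multilevel models of each person's path from before the intervention to twelve months, so baseline enters the planned analysis of change. The protocol gives no information on d_I or d_C, so neither size nor direction can be calculated.

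**4. The responder form.**
Study population requires a low IPAQ level, and Randomisation admits only those who meet the criteria. Every participant's starting category is therefore set before allocation. Moving from low to moderate or high then depends on the follow-up classification, not on a repeated baseline. The difference of 0.15 between proportions in Sample size fits this form.

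**5. The final evaluation.**
The Intervention section has physical activity specialists running the classes. The Blinding section has independent investigators assessing. Nothing says that session leaders collect outcomes or that assessors watch the class, so the two statements can both hold. What remains is the shared occasion, against which the only stated safeguard is asking participants not to disclose their group. The blinding statement covers the end of programme and follow-up; it does not mention the baseline assessor.

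**The case against.** The strongest reply is that the two sections governing sequence are explicit that baseline comes first, and that *first session* is a loose time label in a condensed article. The Control group section supports this in part: its reminder sentence calls the final occasion an assessment session. This has some force. The text does not establish that baseline *will* be taken after allocation, only that the instructions disagree. But the loose reading must be supplied by the reader, and it sits badly with the numbered classes and with inviting people already assigned. A centre following the Intervention and Control group sections would collect a post-allocation baseline.

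The reply is also right that the eligibility IPAQ protects the responder form of the primary outcome, and that laboratory values and visit counts are not self-reported.

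Two stronger readings might be inferred, and the protocol supports neither:
- *The assessor cannot be blind at the last session.* The assessors are independent of the session leaders, and nothing places them in the class. Blinding is at risk, not contradicted.
- *Controls are contaminated by attending exercise sessions.* They are invited to occasions at which parameters are evaluated and told to continue their usual routine. Nothing says they exercise there.

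Finally, participants know their group by design, so self-report bias at follow-up remains whatever is done about baseline.

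**Conclusion.** The contradiction on baseline timing is real and should be corrected. The Randomisation and Blinding sections cannot be followed together with the Intervention, Control group and Other specific objectives sections as worded. If the session-based timing is applied, the estimates at risk are the change in weekly METs and the changes in the self-reported secondary measures; the responder form of the primary outcome is less exposed. The bias cannot be quantified from the protocol. The conclusion assumes that *session* carries the same meaning throughout the Intervention section and that participants can know their group by session 1; the text supports both.

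The last-session evaluation is a secondary risk to assessor blinding. How large it is depends on how the assessment is physically arranged, which the article does not say.

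**What to change.** 1. State once that all baseline measures, including the IPAQ, the questionnaires and the blood tests, are completed before allocation is revealed to participants or staff. Make the Intervention and Control group sections agree with Randomisation and Blinding.
2. In Control group, Physical activity promotion programme and Other specific objectives, replace *first session* with *pre-randomisation baseline visit* and *last session* with *end-of-programme assessment* wherever they time a measurement.
3. State that the blinded independent investigators carry out the end-of-programme assessment of both arms apart from the exercise class.

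The measures, assessors and sample size stay the same. The cost is rewording and some separate appointment slots at each centre. It has to be done before recruitment, because a baseline collected after allocation cannot be repaired afterwards.
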